**Figure 1. SPARKLE enrolment and group allocation procedure.**

1. **Sample**

A total of 616 will be recruited into the trial with 308 consenting parents randomised to each arm following SPARKLE baseline assessments. This sample size was powered to address our primary question whether comparing outcomes at one month post-randomisation, *Parent Positive* will reduce children’s conduct problems observed as compared to FAU. During the first UK lockdown (i.e., March to June 2020) there was around an approximate 0.2 standard deviation increase in SDQ conduct problems scores reported by Co-SPACE parents with children aged 4-10. For the current study, we took this as representing the smallest between group difference that was of clinical value to detect between *Parent Positive* and FAU scores post-randomisation (i.e., Cohen’s *d* of 0.2). We assumed a within trial drop-out rate of 30%, a correlation of 0.5 between one pre- and two post-randomisation measures (Machin, Campbell, Tan, & Tan, 2018), and using a one-tailed (Parent Positive > FAU) and an alpha of .05 that this number of participants provides 90% power to test the one-sided hypothesis that *Parent Positive* is superior to FAU.

1. **Recruitment**

Participants will be recruited into SPARKLE from the pool of Co-SPACE families of children aged 4-10. Recruitment into the Co-SPACE study is ongoing using advertisements on social media and through circulating information about the study to primary schools and relevant organisations, so SPARKLE may also recruit participants that are new to Co-SPACE.

1. **Allocation**

Participants will be enrolled into the study online via the Quatrics platform. Following consenting, simple randomisation will be carried out remotely within the Qualtrics programme using the Randomizer function, after which the parents in the *Parent Positive* group will be given access to the app as in section 7.4 above. Enrolled participants will be allocated to *Parent Positive* or FAU at the ratio of 1:1 by simple randomisation. Neither blocking nor stratification will be used.

1. **Blinding**

It is not possible to blind parents enrolled in the study and Qualtrics will automatically inform parents of their group allocation. Data will be collected remotely by Qualtrics. Blinded members of the research team and the senior statistician will not be given access to the Qualtrics system or the data in order to remain blinded until after the analysis is complete. We do not anticipate any serious harms associated with taking part in the intervention, therefore there will be no need to unblind any blinded staff during the study. The junior statistician will be unblinded throughout.

1. **Data collection**

SPARKLE data will be collected at monthly intervals at three time points following the Co-SPACE schedule as indicated above (Baseline [T1], T2, and T3) using the Qualtrics platform. Finally, in SPARKLE, *Parent Positive* usage data will be collected automatically within the app across the intervention period as described above.

1. **Data management**

Handling of the data collected in Co-SPACE is described in detail in the Co-SPACE Data Management Plan. The SPARKLE Data Management Plan outlines how SPARKLE-specific data collected outside of the Co-SPACE routine follow-ups will be managed and stored during and after the project is completed. The junior statistician will request periodic data extracts from the Co-SPACE (baseline) and SPARKLE (follow-up) teams; these will be shared via a restricted OneDrive for Business link, then moved to King’s College SharePoint location, which is a web-based, Microsoft Office integrated collaborative platform. The data provided from Co-SPACE will be linked to the *Parent Positive* usage data using the SPARKLE ID. The data stored on SharePoint are encrypted and access to the data will be restricted only to those who need to have it.

1. **Statistical analysis**

**Aim i) Does *Parent Positive* reduce the average levels of parent-reported child conduct problems in a self-selected community sample, measured over a one (primary outcome) and two month (secondary outcome) period, when compared to Follow-up As Usual (FAU)?**

**Aim ii) Does *Parent Positive* reduce the average levels of parent psychological distress, parental child-related stress and worries, family conflict and child emotional problems (additional secondary outcomes) in a self-selected community sample, measured over a one and two month period, when compared to FAU**?

Briefly, a mixed effects linear analysis of covariance (ANCOVA) model with repeated measures will be used with **the SDQ conduct problem** scores at one (primary outcome) and two months (secondary outcomes) post-randomisation as the dependent variables, and intervention group, time point, intervention group by time point interaction, baseline SDQ conduct problem score, gender and age of child as independent variables, with the interaction term used to extract the primary and secondary outcome effects at the two time points. Similar statistical models will be used to test for intervention effects on the other secondary outcome scale scores (average levels of parent psychological distress, parental child-related stress and worries, family conflict and child emotional problems) at one and two months post-randomisation. All analysis will follow the intention to treat (ITT) principle as far as possible (Sullivan et al., 2018; White et al., 2012).

**Aim iii) Are the effects of *Parent Positive* on the primary conduct problem outcome** **moderated by levels of (i) pre-existing levels of conduct problems (subgroup analysis) and (ii) *Parent Positive* usage levels as monitored during the one month intervention period (post-randomisation intervention** **effect modification analysis).**

As for the concept of adherence, the concept of per protocol analysis seems less sensible in this trial where the intervention is taking more of a public health approach with no specific direction of how and when to use, in a sample not restricted to those with a specific clinical need. In this sense, and for this particular intervention, there is not a “intervention protocol” that parents need to adhere to. However, an analysis of the extent to which effects depend on (i) pre-existing levels of child conduct problems and (ii) intervention uptake will help to interpret the value of the app. To address (i) in the mixed model for conduct problems described under Aims i and ii, the intervention by time interaction term will be replaced with an intervention by time by baseline conduct problems interaction. Intervention effects for different conduct problem scores will be extracted at the two time points. To address (ii) the effect of the app usage measure, total time accessing the Boosters zone during the one month intervening period, will be assessed using appropriate causal methods for post-randomisation variables measured only in the Parent Positive group (Dunn et al., 2015). Child gender and age will be entered as independent variables, as well as other variables that could be predictors of app usage (i.e., pre-existing levels of conduct problems). Usage of *Parent Positive* will be monitored for two months for descriptive purposes.

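### The stated 90% power is for the average of the one- and two-month scores; for the one-month primary outcome the same assumptions give about 77%

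*Protocol*

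**What the plan says.** The Sample section of the protocol sets the target at 616 parents, 308 per arm, and ties it to a single time point: "This sample size was powered to address our primary question whether comparing outcomes at one month post-randomisation". The inputs are a standardised difference of 0.2, which the section treats as the smallest worth detecting, 30% drop-out, "a correlation of 0.5 between one pre- and two post-randomisation measures", and a test "using a one-tailed (Parent Positive > FAU) and an alpha of .05". It concludes that "this number of participants provides 90% power to test the one-sided hypothesis".

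The rest of the protocol is consistent about the primary time point. Objectives (first aim) and Measures and Outcomes (conduct problems) make the one-month SDQ conduct score primary and the two-month score secondary. The Statistical analysis section (Aims i and ii) fits a repeated-measures ANCOVA with group, time, group by time, baseline score, child gender and child age, "with the interaction term used to extract the primary and secondary outcome effects at the two time points". Nowhere is the average of the two follow-ups made the primary effect. The references to average levels in the aims mean group mean scores, since one month and two months are labelled separately beside them.

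**The concern.** The sample size calculation takes credit for two follow-up measures, while the effect it is meant to support uses one. Averaging two follow-up scores reduces the variance of the treatment effect, but only if that average is what is tested. Once the model includes a group-by-time interaction and the one-month effect is read off separately, the two-month score adds almost nothing to its precision.

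At stake is how the trial is read. A null primary result would be taken to come from a trial with a 10% chance of missing the difference the protocol calls worthwhile. If that chance is more than twice as large, the result supports a weaker conclusion than readers will draw. The treatment estimate and the type I error rate are not affected.

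**Working it through.** **Inputs (Sample section).** d = 0.2 with SD 1; one-sided alpha 0.05 (z = 1.6449); power 90% (z = 1.2816); correlation ρ = 0.5; one baseline and two follow-ups; 30% drop-out; 1:1 allocation.

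**1. Reproduce 308 per arm.** Without baseline adjustment or repeated measures, the number per arm is 2(1.6449 + 1.2816)²/0.2² = 428.2.

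For one baseline and w follow-ups with equal correlation ρ, the ANCOVA variance factor for the mean of the follow-ups is R = [1 + (w − 1)ρ]/w − ρ².

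- With w = 2: R = 1.5/2 − 0.25 = 0.50.
- 428.2 × 0.50 = 214.1, rounded up to 215.
- 215/0.7 = 307.1, rounded up to 308 per arm, 616 in total.

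The match is exact. The other readings tried do not give 616:

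| Reading | Total |
|---|---|
| One baseline, one follow-up | 920 |
| No baseline, one follow-up | 1,226 |
| One baseline, two follow-ups, two-sided | 752 |
| As the protocol, but 215 × 1.3 for drop-out | 560 |

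**2. What the factor 0.50 measures.** Given the baseline score, each follow-up has variance 1 − 0.25 = 0.75, and the two have covariance 0.5 − 0.25 = 0.25. The mean of the two has variance (0.75 + 0.75 + 2 × 0.25)/4 = 0.50. The one-month score alone has variance 0.75.

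**3. Power for the one-month effect.** With 215 per arm:

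- Average of both follow-ups: Φ(0.2/√(2 × 0.50/215) − 1.6449) = Φ(1.288) = 0.901.
- One month alone: Φ(0.2/√(2 × 0.75/215) − 1.6449) = Φ(0.750) = 0.773.

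**4. Detectable difference and required size at one month.**

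- Difference detectable with 90% power: (1.6449 + 1.2816) × √(2 × 0.75/215) = 0.244 SD.
- For 90% power at 0.2 SD: 428.2 × 0.75 = 321.1, rounded up to 322; 322/0.7 = 460 per arm, 920 in total.

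**5. Does the mixed model recover the loss?** Under the same correlations, if the same 30% miss both follow-ups, the interaction model gives 77.4% for the one-month effect and 90.2% for the average (using 308 × 0.7 = 215.6 per arm). If 30% are missing independently at each visit, the two-month score helps a little through those who missed one month, and one-month power is 78.3%. A simulation of the mixed ANCOVA (308 per arm, 30% loss, 2,000 runs) gave 77.9% and 90.4%.

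**6. Sensitivity of one-month power.**

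| Loss by one month (ρ = 0.5) | 30% | 25% | 20% | 15% | 10% | 0% |
|---|---|---|---|---|---|---|
| Power | 77.4% | 79.9% | 82.1% | 84.1% | 85.9% | 88.9% |

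| ρ, baseline to one month (30% loss) | 0.5 | 0.6 | 0.7 | 0.71 |
|---|---|---|---|---|
| Power | 77.4% | 82.9% | 89.7% | 90.4% |

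At 30% loss, 1 − ρ² must fall to 0.50 to restore the planned 90%, so ρ must be √0.50 = 0.71.

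**The case against.** The best objection is that the real shortfall may be smaller. The 30% is given as drop-out for the trial as a whole, and follow-up runs to two months, so fewer parents may be lost by one month. The correlation of 0.5 may also be cautious. In Measures and Outcomes the protocol reports retest values among Co-SPACE parents of .71 for the stress and worries scale and .73 for family conflict. If SDQ conduct scores behaved similarly, one-month power would be about 90% even at 30% loss. Smaller departures in both together would also do it: at 20% loss (246.4 per arm) and ρ = 0.65, Φ(0.2/√(2 × 0.5775/246.4) − 1.6449) = 0.90.

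This makes 77% a conditional figure, and 0.71 is the correlation needed only when loss is 30%. It does not rescue the statement as written. The protocol assumes 0.5, gives no one-month loss rate, and reports no retest value for SDQ conduct problems; the two it gives belong to other scales. At its own correlation, power stays below 90% even if nobody drops out.

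It can also be said that nothing is biased and that a null result can be judged from its confidence interval. That is true, but the 90% remains a wrong figure for the only primary outcome.

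**Conclusion.** The concern holds. The 90% belongs to the effect averaged over one and two months, while the protocol defines and analyses its primary outcome at one month only. Under its own assumptions (d = 0.2, one-sided alpha 0.05, ρ = 0.5, and the full 30% lost by one month), power for the primary outcome is about 77% and the chance of missing the target difference about 23%. The detectable difference of 0.24 SD exceeds the 0.2 SD the protocol set as worthwhile. Lower early loss would raise power to between 79.9% (25% lost) and 88.9% (none lost). Only a higher correlation, alone or together with lower loss, would bring it to 90%.

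**What to change.** Rewrite the power paragraph in the Sample section for the one-month contrast, using the factor 1 − ρ² for a single follow-up.

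- Restate power as about 77% at ρ = 0.5 with 30% loss, and the difference detectable with 90% power as 0.24 SD.
- Estimate ρ for SDQ conduct problems one month apart from the monthly Co-SPACE data already held, and show power over ρ from 0.5 to 0.7.
- State the loss assumed by one month separately from the loss by two months.

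The sample size can stay at 616. The cost is one paragraph and a less favourable power figure, unless the Co-SPACE correlation turns out to be about 0.7. Two other routes would also remove the contradiction, at a higher price: making the one- and two-month average the primary effect, which changes the primary outcome, or recruiting about 920 to keep 90% at one month under the stated assumptions.

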     1. **Parental child-related stress and worries levels (T1 co-variate; T2 and T3 secondary outcomes):** This is based on five items routinely measured in Co-SPACE regarding children’s behaviour, wellbeing, screen time use, education and future using a 4-point Likert scale (not at all, a little, quite a lot, a great deal). Individual questions’ scores are summed to generate a single score. The scale has an adequate level of internal consistency (Cronbach alpha > .70) and re-test reliability (*r* = .71) amongst Co-SPACE parents.
     2. **Family conflict (T1 co-variate; T2 and T3 secondary outcomes):** This is based on three items routinely collected in Co-SPACE relating to arguments between parents, parents and children and siblings which are measured on a 4-point Likert scale (not at all, a bit, a lot, completely). The three questions are summed to generate a total score. The scale has acceptable internal consistency (Cronbach alpha > .54) and test-retest reliability (*r* = .73) amongst Co-SPACE parents.
     3. **Parental psychological distress (T1 co-variate; T2 and T3 secondary outcome; T1 moderator):** The Depression, Anxiety and Stress Scales-21 (DASS-21) is a widely validated 21-item self-report questionnaire measuring adult depression, anxiety and stress (Lovibond & Lovibond, 1995). Each of these three subscales consists of seven items rated on a 4-point Likert scale (did not apply to me at all; applied to me to some degree, or some of the time; applied to me to a considerable degree, or a good part of the time, applied to me very much, or most of the time), which are summed to obtain a single subscale score. The subscales scores will be summed and multiplied by two to form a single psychological distress measure comparable to the DASS-42 measure.
  2. **Other measures**
     1. **ADHD symptoms (T1 moderator; T1, T2 and T3 for QALYs calculation)**: measured with the inattention/overactivity subscale of the SDQ (Goodman, 1997). This five-item subscale measures restlessness, overactivity and inattention rated on 3-point Likert scales (not true, somewhat true, and certainly true), with a mix of positive and negatively phrased items. Individual items’ scores are summed to derive an overall symptoms subscale score.

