     6. **App usage data (During intervention period, intervention arm only):** Usage data will be broken down by *Parent Positive* elements (challenges) and domains (Boosters, Exchange, Resources). This will allow descriptive analysis of usage patterns. The analysis of the impact of usage levels on the effects of *Parent Positive* (see analysis section below) variables will be based on a derived measure of total time accessing the “Boosters” zone during the one month intervening period. Other app usage metrics will be collected (e.g., engagement in Exchange zone).
     7. **Family characteristics and demographic measures (T1 co-variates; sample description):** Parents will provide information about their child’s age and gender, their own and their child’s ethnicity, number of children in the family, number of rooms in the family home and access to outside space. This information will be used to describe the sample and an overcrowding index will be calculated by dividing the number of individuals in the household by the number of rooms. We will estimate family SES based on total household income, coded as < £16,000 | £16,000 - £29,999 | £30,000 - £59,999 | £60,000 - £89,999 | £90,000 - £119,999 | > £120,000 | Prefer not to say, likely collapsing small categories.
     8. **COVID-19 pandemic lockdown circumstances (T1 moderator; T2 descriptives; T3 descriptives):** Parents will provide information on the pandemic-related restrictions they are currently facing. This will include details of the current lockdown policy in their local area (partial or full lockdown), whether parents are working from home, and whether children are being home-schooled.

1. **Time schedule of enrolment and assessment**

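### The conduct model adjusts only for baseline conduct, child gender and child age; adding baseline parental distress would protect the one-month effect against dropout that depends on distress differently by arm, at almost no cost

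*Protocol*

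**What the plan says.** **Model.** Under Aims i and ii, the Statistical analysis section describes a repeated-measures mixed model with arm, time point, their interaction, and "baseline SDQ conduct problem score, gender and age of child as independent variables". The other outcome scales get similar models. Analysis is by intention to treat as far as possible, with two methodological citations on missing data.

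**Family block.** The Other measures section heads this block "Family characteristics and demographic measures (T1 co-variates; sample description". It opens: "Parents will provide information about their child’s age and gender, their own and their child’s ethnicity, number of children in the family". It then says "This information will be used to describe the sample and an overcrowding index will be calculated" and "We will estimate family SES based on total household income".

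**Distress.** The Parent/family outcome section labels it "Parental psychological distress (T1 co-variate; T2 and T3 secondary outcome; T1 moderator". Conduct problems, emotional problems, stress and worries, and family conflict carry the same kind of T1 covariate label.

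**Dropout and blinding.** The Sample section says "We assumed a within trial drop-out rate of 30" per cent. The Blinding section says that parents are told their allocation. FAU parents receive no app for the first 10 weeks and full access afterwards.

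**The concern.** A likelihood-based mixed model handles dropout correctly when missingness depends only on the terms in the model and on observed outcomes. A parent who misses both follow-ups contributes no outcome, so only baseline conduct, gender and age can account for that loss. An unblinded comparison of an app with nothing could plausibly hold hard-pressed parents in one arm and lose them in the other. If distress also carries information about later conduct that baseline conduct does not, the completers in the two arms are no longer comparable given the model's covariates. The bias can go either way. It dilutes the effect if distressed parents stay with the app and leave FAU, and exaggerates it in the reverse case. The variable needed to guard against this is already collected at T1.

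**Working it through.** **1. The plan's own figure.** Inputs from the Sample section: difference 0.2 SD, one-sided alpha 0.05, power 90%, "a correlation of 0.5 between one pre- and two post-randomisation measures", dropout 30%.
- Variance factor: (1 + 0.5)/2 − 0.5² = 0.50.
- Evaluable per arm: 2 × 0.50 × (1.645 + 1.282)² / 0.2² ≈ 214.1, or 215 rounded up.
- Randomised per arm: 215/0.7 = 307.1, or 308. The total is 616, as stated.

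**2. Standard error at one month.** Evaluable per arm: 308 × 0.7 = 215.6. A single follow-up adjusted for baseline has variance factor 1 − 0.5² = 0.75. The SE is √(2 × 0.75/215.6) = 0.083 SD.

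**3. Form of the bias.** Let b be the slope of one-month conduct on T1 distress given baseline conduct. Let Δ be the difference between arms (app minus FAU) in mean distress among completers, given baseline conduct. Then bias = b × Δ. If either is zero, there is no bias.

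**4. Size under assumptions.** None of the following inputs is in the protocol: T1 distress and T1 conduct correlate 0.3; b is 0.10 to 0.25; dropout is logistic in distress and calibrated to 30% in each arm. The true effect is −0.20 SD and the pre–post correlation is 0.5, as in the Sample section. The check is a large-sample simulation of the one-month ANCOVA in completers.

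| b | Log-odds slope 0.4 in FAU only, or −0.2 app / +0.2 FAU (Δ ≈ 0.107) | −0.4 app / +0.4 FAU (Δ ≈ 0.212) |
|---|---|---|
| 0.10 | 0.011 | 0.021 |
| 0.15 | 0.016 | 0.032 |
| 0.20 | 0.021 | 0.042 |
| 0.25 | 0.027 | 0.053 |

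The stated model therefore estimates about −0.19 to −0.15. With T1 distress added, the estimate returns to −0.20 within simulation error (−0.197 to −0.203).

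**5. Same relation in both arms.** With slope 0.4 in both arms Δ is zero and so is the bias. A separate run with slopes 0.5 or 1.0 in both arms gave biases between −0.0014 and +0.0004 SD.

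**6. Reverse direction, steeper slopes.** Here distress correlates 0.3 or 0.4 with conduct at both times. For 0.3, b = (0.3 − 0.3 × 0.5)/(1 − 0.3²) = 0.165; for 0.4, b = 0.238. The app arm loses the distressed parents, with slopes differing by 0.5 to 1.0. The effect is then exaggerated by 0.023 to 0.059 SD.

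**7. Effect modification.** If the effect changes by −0.1 SD per SD of distress and the dropout slope is 0.5 in both arms, the stated model gives −0.186 and the adjusted model −0.187. Adding the main effect does not help.

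**8. Gain without differential dropout.** The share of residual variance removed is b²(1 − 0.3²)/0.75, which is 0.012 for b = 0.10 and 0.076 for b = 0.25. Among completers the simulated variance ratio is 0.93 to 0.99, a reduction of about 1% to 7%.

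**9. Consequence for the test.** Under no true effect, a favourable bias of 0.01 to 0.05 SD shifts the test statistic by 0.01/0.083 = 0.12 to 0.05/0.083 = 0.60. The one-sided 5% error becomes 1 − Φ(1.645 − 0.12) ≈ 6% to 1 − Φ(1.645 − 0.60) ≈ 15%.

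**Limits.** Income was not simulated. The simulation uses the one-month outcome only; the mixed model recovers some information from parents who miss one month but return at two.

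**The case against.** The strongest reply is that the stated model is a valid prespecified choice. Adjusting for the baseline outcome, age and gender is normal in an unstratified trial. The bias rests wholly on assumed correlations and slopes, and even its upper end is below the standard error of 0.083 SD. The upper end also needs distressed parents to be held in one arm and lost in the other, which the protocol does not suggest. The promise of the app after follow-up may keep FAU parents in. All of this stands, and it is why the point is not an error in the plan.

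Four stronger readings are tempting and are not supported:

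- **Any dropout related to distress or income biases the effect.** It does not. The relation must differ by arm (step 5), or distress must modify the effect, which the remedy does not cure.
- **The protocol gives two conflicting covariate sets.** Child age and gender belong to the family block and are in the model. The label covers both covariates and sample description, and the text gives description as the use of the information. This is a loose label.
- **DASS-21 was declared a covariate for the conduct model.** Its label matches that on the other outcome scales and most naturally refers to its own outcome model. That model already contains baseline distress, so not every secondary outcome is exposed.
- **Predictors of dropout are ignored.** They may enter through multiple imputation, the subject of one of the cited papers. A protocol commonly leaves that to the SAP, which is not available here, so silence on it is no finding.

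What the reply does not remove is that the protocol itemises the model terms, and that one more pre-randomisation covariate would close a plausible route to bias at negligible cost.

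**Conclusion.** The point holds as a cheap improvement to the itemised covariate list. The one-month effect can be biased by about 0.01 to 0.05 SD, roughly 5% to 25% of the 0.2 SD target. This requires both that dropout depends on distress differently by arm and that distress predicts one-month conduct beyond baseline conduct. Both are assumptions: plausible with 30% expected loss and unblinded arms, but not shown by the protocol. The direction is not known in advance. Where the two conditions fail, the adjusted model loses nothing that matters and may gain a little precision. The family-characteristics label needs only a wording change.

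**What to change.** 1. In the Statistical analysis section, add T1 DASS-21 total as a prespecified fixed covariate in the conduct model and in the models for emotional problems, child-related stress and worries, and family conflict. The DASS-21 model already has it.
2. Keep the present model (baseline score, gender, age) as a sensitivity analysis.
3. Household income band may be added, with non-disclosure as its own level. This is optional, since its effect was not examined.
4. In the Other measures section, let the covariate label name exactly the family variables that enter the model (at present child age and gender) and mark the rest as descriptive.
5. Make these changes before any outcome data by arm are examined.

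**Cost.** Wording only, with no new data. About one degree of freedom is spent out of some 431 evaluable parents (616 × 0.7). A rule is needed for the few baseline DASS-21 scores still missing after the protocol's prorating; filling in the overall baseline mean, calculated without regard to arm, would do. The change does not protect against dropout combined with effect modification by distress, and the report should say so.
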